#### ✓ Primary objective

To estimate :

- **Accuracy of shootings** on a precise area (step 1) then on a zone to be spared (step 2),  
 ↳ THROUGH: both the distance between the hurt epicentre generated by hifu and a mark (step 1) and between the hurt limit and a vessel border previously marked (step 2). These sizes will be measured in mm during anatomopathological exam.

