#### **✓ Shootings process**

##### **⇒ Phase I**

The shootings will concern the healthy liver to remove, distant to the important vascular structures and metastases. Two HIFU shootings will be made on each patient:

- One hurt on the surface starting from the Glisson capsule and extending to subjacent hepatic parenchyma.
- One hurt at given depth, at least 10 mm deeper than the hurt done on the surface

NB: The shooting depth will be determined for each patient at the beginning of the operation, considering preoperative exams (scans, etc.), size and location of the liver part to be resected and physical structure of the patient.

⇒ **Phase IIa**

The shootings will concern healthy liver to be resected, distant (step 1) then close (step 2) to the important vascular structures of the liver. Several shootings HIFU will be made on each patient (ideally 4 hurts, minimum 2 hurts)

Step 1

Each mark will be spotted by a stationary mark set at a given depth (1st hurt on liver surface, 2nd hurt at depth of  $40 \pm 5$  mm, 3rd hurt at  $20 \pm 5$  mm, 4th hurt at  $60 \pm 5$  mm). Shootings will be performed by superimposing the theoretical hurt epicentre and the mark (the mark will have to be included in the generated hurt)

Step 2

Vascular structures will be colored in Patent Blue or Methylene Blue and will work as a mark. Shootings will be performed by positioning the closest theoretical hurt limits to a vessel at a distance of 5 to 10 mm from the vessel border.

⇒ **Phase IIb**

Shootings will concern small metastases ( $\leq 20$  mm) and peri lesional healthy liver. They will be juxtaposed on multiple plans in order to generate a large hurt containing the metastasis targeted and guaranteeing a sufficient safety margin in healthy liver. Several metastases can be treated in the same patient

✓ **Immediate following of the intervention**

The whole abdominal cavity will be explored to detect possible adverse effects, especially burns, involving adjacent organs to liver.

Once HIFU delivered the hepatectomy procedure will be totally identical to the one that would have been done if patient would not have received HIFU shootings.

The anatomopathological analysis will include, in addition, an analysis of each of the HIFU hurts.

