#### VI.1.b. Phase II

##### ✓ Phase IIa

**A group of 6 to 12 patients** will be included in 2 sequential steps with 3 to 6 patients in each. This number of selected patients has been defined by a classic dose escalation method used in clinical trials. The goal is to bring to light an insufficient accuracy of HIFU shootings if this event arises with a high frequency. Based on the binomial distribution, groups of respectively 3 and 6 patients allow a  $90\%$  probability to get at least one patient receiving an unacceptable shooting (inaccuracy), if this event occurs respectively in at least  $54\%$  and  $32\%$  of the cases.

[figure not shown]

• **1st step** (3 to 6 patients) :

A success is defined for one patient in a given amount of shootings ( $2 \leq n \leq 4$ ), if the mean distance between the closest hurt limit to the mark and the mark itself is  $< 5$  mm. Otherwise, the event will be considered as a failure.

3 patients will be included in the 1st step:

- If no failure is noticed → proceed to step 2;
- If 1 or 2 failure is(are) noticed 3 more patient are included in first step.
  - ↳ If  $> 2$  failures out of 6 → the study is stopped,
  - ↳ If  $\leq 2$  failures out of 6 patients → proceed to 2nd step
- If 3 failures are noticed → the study is stopped.

[figure not shown]

• **2nd Step** (3 to 6 patients) :

A success is defined for one patient in a given amount of shootings ( $2 \leq n \leq 4$ ), if the mean distance between the closest hurt limit to the vessel mark and the vessel it-self is  $\geq 5$  mm and  $< 10$  mm. Otherwise, the event will be considered as a failure.

3 patients will be included in the 1st step:

- If no failure is noticed → proceed to phase IIb;
- If 1 or 2 failure is(are) noticed, 3 more patient are included in first.
  - ↳ If  $> 2$  failures out of 6 → the study is stopped,
  - ↳ If  $\leq 2$  failures out of 6 patients → proceed to phase IIb,
- If 3 failures are noticed → the study is stopped.

NB: At the conclusion of the phase IIa, the Steering committee of the study will meet to examine all the brought together data, validate or not the criteria of continuation of the study and define more exactly the methodology of the phase IIb.

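### Phase IIa step 2 scores each patient on a mean distance alone, so a hurt that reaches the vessel can be offset by the other shots and the patient counted as a success

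*Protocol*

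**What the plan says.** Phase IIa has one primary objective, accuracy of the shots: first on a precise area, "then on a zone to be spared (step 2") (Protocol III.2.a).

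The shootings process in Protocol IV.2.c gives each phase IIa patient several hurts ("ideally 4 hurts, minimum 2 hurts"). In step 2 each shot is placed with the "closest theoretical hurt limits to a vessel at a distance of 5 to 10 mm from the vessel border".

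The scoring rule is in Protocol VI.1.b: "A success is defined for one patient in a given amount of shootings", from 2 to 4. In step 2 the criterion is that "the mean distance between the closest hurt limit to the vessel mark and the vessel it-self" is at least 5 mm and below 10 mm; any other result is a failure. Three patients are treated first. No failure leads to phase IIb, three failures stop the study, and one or two failures add three patients, with continuation if at most 2 of the 6 have failed.

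The same section justifies groups of 3 and 6 by a 90% probability of "at least one patient receiving an unacceptable shooting (inaccuracy") when that event occurs in 54% and 32% of cases.

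Step 1 also uses an average: "the mean distance between the closest hurt limit to the mark and the mark itself" must be below 5 mm.

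**The concern.** Sparing a vessel is a matter of closest approach, and a mean does not record closest approach. A hurt on the vessel border and a hurt far from it can average to a value inside the window, and the patient is then an accuracy success. Each shot is aimed at 5 to 10 mm, but no shot has to land there.

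The sample-size rationale points the same way. On its natural reading, a patient who receives an unacceptable shot is someone with at least one bad shot. Under the mean rule that patient need not be a failure, so the quoted 90% chance of detection need not carry over to the decision.

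Step 2 is the last count-based decision before shots are placed around metastases. What is at stake is a wrong accuracy conclusion and a wrong decision to continue.

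**Working it through.** **1. The plan's own figures.** The event rate giving a 90% chance of at least one event in n patients is 1 − 0.10^(1/n).
- n = 3: 53.6%; n = 6: 31.9%.
- Check: 1 − 0.46³ = 90.3% and 1 − 0.68⁶ = 90.1%.

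The stated 54% and 32% are right as arithmetic. The question is which event they describe.

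**2. What the mean rule lets through, without assumptions.** If one of k shots is at 0 mm, the patient passes when the other shots average from 5k/(k − 1) to below 10k/(k − 1) mm.

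| Shots | Mean needed from the other shots | Example | Patient mean | Scored |
|---|---|---|---|---|
| 2 | 10 to <20 mm | 0, 14 | 7.00 mm | success |
| 3 | 7.5 to <15 mm | 0, 8, 8 | 5.33 mm | success |
| 4 | 6.7 to <13.3 mm | 0, 7, 7, 7 | 5.25 mm | success |

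With 2 shots the compensating shot must itself be outside the window. With 3 or 4 shots, ordinary in-window shots are enough.

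**3. Illustration of size.** The Protocol gives no SD for shot distances, so these values are assumed. Model: distance = max(0, aim + error), aim uniform on 5 to 10 mm, error Normal(0, SD), simulated with at least 300,000 patients per setting. With 4 shots:

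| SD (mm) | Single shots in window | Patients scored success | Successes with a shot <5 mm | Successes with a vessel contact |
|---|---|---|---|---|
| 1 | 84% | >99% | 28% | 0% |
| 2 | 68% | 96% | 50% | 0.2% |
| 3 | 55% | 87% | 66% | 4% |
| 4 | 44% | 77% | 77% | 12% |
| 5 | 37% | 69% | 85% | 25% |

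A second model with every aim at 7.5 mm gives the same picture. For SD 3 to 5 mm, a patient with at least one vessel contact is still a success in 20 to 31% (2 shots), 50 to 52% (3 shots) and 65 to 69% (4 shots) of cases.

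**4. Number of shots.** For a device centred in the window (first model, SD 4 mm), patient success is 60% with 2 shots and 77% with 4. With success probability q and f = 1 − q, the chance of passing step 2 is q³ + 3q²f(q³ + 3q²f) + 3qf²·q³. This gives 56% with 2 shots and 87% with 4 for the same device.

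**5. A device that is systematically too close.** With distances Normal and floored at 0, 4 shots and SD 2 to 4 mm, a device centred at 3 mm passes step 2 in at most about 1.5% of trials. Centred at 4 mm, it passes in about 1% (SD 2) to 12% (SD 4).

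**The case against.** **The word shooting may refer to the patient.** The binomial counts patients, so an unacceptable shooting could mean a patient who fails the defined mean criterion. The 54% and 32% would then fit the decision rule. This reading is possible, so the mismatch with the sample-size text is a supporting argument only. The counter-examples do not need it.

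**There are other safeguards.** The shots fall in liver that will be resected. The Steering committee examines all data after phase IIa and may decline to continue. Minimum and maximum values are reported, and phase IIb requires its margin at every point. These limit the consequences, but none changes the success count in step 2. The phase IIa safety criterion lists peripheral tissues and does not include the intrahepatic vessel.

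**The illustration is sensitive to its inputs.** Aims spread down to exactly 5 mm inflate the count of shots under 5 mm: even at SD 1 mm it is 28%, with no contacts. The percentages show a range and are not estimates for this device.

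**Stronger readings that a reader might infer, and that do not hold:**
- That a contact is always cancelled. It can be; this depends on the other shots.
- That the rule passes a device that is habitually too close. Step 5 shows that it mostly does not.
- That more shots always make success easier. This is true only for a device centred in the window. With a true mean of 3 mm (SD 4 mm), success falls from 24% with 2 shots to 18% with 4; with a true mean of 12 mm, from 23% to 16%.
- That step 1 has the same fault. Its distances to the mark are unsigned, so one miss is diluted by the other shots and not offset by an opposite error.

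**Conclusion.** The step 2 success rule is wrong as written. It can score as accurate a patient in whom a hurt reached the vessel, and this follows from arithmetic alone. The weakness is specific: it concerns a device that is right on average but variable from shot to shot. For such a device the result also depends on whether 2 or 4 shots were given.

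The size depends on an SD that the Protocol does not state. With 4 shots, evenly spread aims and SD 1 to 5 mm, 28 to 85% of successes contain a shot under 5 mm and 0 to 25% a vessel contact. If the true SD is 2 mm or less, contacts hidden among successes are rare. Step 1 is a lesser matter.

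**What to change.** In Protocol VI.1.b, step 2:
- Score each shot against both of the plan's own limits (at least 5 mm and below 10 mm), and do not let the mean alone decide. The sponsor should state the per-shot condition that makes a patient a success. At the least, a patient with a hurt reaching the vessel border should not be a success, whatever the mean.
- Keep the upper limit. A rule on the smallest distance alone would pass a device landing on average 20 mm away (SD 4 mm) about 100% of the time. It would also reverse the dependence on shot count: at SD 4 mm, patient success is 52% with 2 shots and 27% with 4.
- Fix the number of shots, or score the proportion of shots within limits, so that patients with 2 and 4 shots are judged alike.
- Recheck the rule for 3 then 6 patients under the new criterion.
- Record the planned distance of each shot, report achieved minus planned, and keep the mean as descriptive.

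The hurt-to-vessel distances are already to be measured at pathology, so no new data are needed apart from the planned distance. The cost is more failures. With 4 shots and assumed SD 3 mm, requiring every shot to be at least 5 mm lowers patient success from 87% to 36% and the chance of passing step 2 from 97% to 14%. Requiring every shot to meet both limits would lower it further. Adding only a no-contact condition to the mean lowers it to 95%. The stopping rule therefore has to be reset together with the criterion.

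For step 1, first reconcile the distance from hurt limit to mark in VI.1.b with the distance from epicentre to mark in the synopsis and III.2.a. Only then consider changing its averaging.

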## ✓ **Phase IIb**

[figure not shown]

A group of 20 patients will be included in this phase. This number has been defined as following:

- The statistical unit for analysis is the metastasis,
- Fleming-A'Hern's method was formerly developed for phase II studies without steps (30) and has been used to determine the number of metastasis to target. A success is defined by a hurt encompassing the metastasis and guaranteeing safety margin  $\geq 5$  mm from any point, within a maximum of 15 shots.

The next hypotheses are used, in which P is the success probability:

- $p_0 = 0,70$  is the superior limit value of success rate which, if met, would mean that HIFU are inefficient on metastases to be resected and peri lesional healthy liver.
- $p_1 = 0,90$  is the inferior limit value of success rate which, if met, would mean that HIFU are efficient to treat metastases to be resected and peri lesional healthy liver.

Given a 5 % alpha risk and an 80 % statistical power, 28 metastases will have to be targeted by HIFU to conclude unilaterally. Assuming that about 1,5 metastases will be targeted on each included patient, that is to say nearly 20 patients.

A count of successes  $\geq 24$  enables to reject  $H_0$  in favour of  $H_1$ .

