**STATISTICAL METHODS**

32 to 38 patients will be included (phase I : 6 patients, phase Iia : 6 to 12 patients, phase IIb : about 20 patients).

For each phase, analyses will be achieved in the selected population to evaluate the clinical feasibility, the tolerance and the efficacy in CLM treated by HIFU. This population concerns all the patients included in the study and who underwent a hepatectomy. The data analysis will be mainly

---

descriptive.

An interim analysis will be given to the Steering committee in charge of the study.

This Committee will meet to make the necessary decisions as for the continuation of the study according to its progress, in agreement with the Sponsor.

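### The Phase IIb cut-off of 24 successes fits exactly 28 metastases, but the planned 20 patients are expected to yield 30 and no rule links the cut-off to the number treated

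*Protocol*

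**What the plan says.** Protocol section VI.1.b, Phase IIb, uses an exact single-stage design with the metastasis as the statistical unit. The null rate is 0.70, which "is the superior limit value of success rate which, if met, would mean that HIFU are inefficient". The alternative is 0.90, which "is the inferior limit value of success rate which, if met, would mean that HIFU are efficient". The error rates are set by "Given a 5 % alpha risk and an 80 % statistical power", and the resulting size is in metastases: "28 metastases will have to be targeted by HIFU to conclude unilaterally". The null hypothesis is rejected at 24 or more successes, and the sentence that says so gives no denominator.

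Enrolment is set in patients: "A group of 20 patients will be included in this phase", or in the synopsis, "phase IIb : about 20 patients". The link between the two units is "Assuming that about 1,5 metastases will be targeted on each included patient, that is to say nearly 20 patients".

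Three other places bear on the count:
- Section IV.2.c allows several metastases to be treated in one patient and sets no maximum.
- Section VI.2 analyses every included patient who could have the hepatectomy and drops only those who could not.
- The notes at the end of the Phase I and Phase IIa rules let the steering committee specify the Phase IIb method more exactly after Phase IIa.

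**The concern.** A fixed success count controls the type I error only for the number of units it was computed for. Here the recruited unit is the patient and the tested unit is the metastasis, so the number tested is not under direct control. The protocol's own conversion points to 30, not 28. Each metastasis beyond 28 makes 24 successes easier to reach, and each one short of 28 makes it harder.

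This is the only test in the protocol with a stated alpha and power. It decides whether the device is called efficient on metastases. A device with a true success rate of 0.70 could pass more often than the stated 5%, or a device at 0.90 could fail more often than the stated power implies.

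**Working it through.** **Inputs from the protocol (section VI.1.b, Phase IIb).** p0 = 0.70, p1 = 0.90, one-sided alpha 5%, power 80%, n = 28 metastases, cut-off r = 24, 20 patients, about 1.5 metastases per patient.

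**Formula.** For n independent metastases, the probability of rejecting is P(X ≥ r) with X ~ Binomial(n, p). Alpha uses p = 0.70 and power uses p = 0.90.

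**Step 1: reproduce the design.** The smallest n for which some r gives P(X ≥ r | 0.70) ≤ 0.05 and P(X ≥ r | 0.90) ≥ 0.80 is n = 28 with r = 24. Alpha is 0.0474 and power 0.8579. The stated figures are correct.

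**Step 2: patients to metastases.** 28/1.5 = 18.7 patients. 19 × 1.5 = 28.5. 20 × 1.5 = 30.

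**Step 3: hold the cut-off at 24 and vary n.**

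| Metastases counted | Alpha (p = 0.70) | Power (p = 0.90) |
|---|---|---|
| 26 | 0.7% | 51.1% |
| 27 | 2.0% | 71.8% |
| 28 | 4.7% | 85.8% |
| 29 | 9.3% | 93.6% |
| 30 | 16.0% | 97.4% |
| 31 | 24.5% | 99.0% |

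The 16.0% at n = 30 needs only the protocol's own inputs, plus the condition that all 30 are counted and 24 is kept.

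**Step 4: let the number vary (assumed distributions).** The protocol gives a mean per patient but no distribution. Two were assumed, both with mean 1.5: A, one or two metastases per patient at 50/50; B, one, two or three at 60/30/10%. The alpha of step 3 is averaged over the resulting total, with the cut-off kept at 24.

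| Evaluable patients | Alpha, A | Alpha, B |
|---|---|---|
| 20 | 19.9% | 22.0% |
| 19 | 10.8% | 13.3% |
| 18 | 4.9% | 7.1% |

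With 20 evaluable patients, exactly 28 metastases occur in only 12% (A) or 11% (B) of trials.

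**Step 5: cut-offs by attained number.** For each n, take the smallest r with P(X ≥ r | 0.70) ≤ 0.05.

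| n | Cut-off | Alpha | Power |
|---|---|---|---|
| 26 | 23 | 2.6% | 74.1% |
| 27 | 24 | 2.0% | 71.8% |
| 28 | 24 | 4.7% | 85.8% |
| 29 | 25 | 3.8% | 84.2% |
| 30 | 26 | 3.0% | 82.5% |
| 31 | 27 | 2.4% | 80.7% |
| 32 | 28 | 1.9% | 78.9% |
| 33 | 28 | 4.1% | 89.4% |
| 34 | 29 | 3.3% | 88.2% |

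Averaged over A or B with 20 evaluable patients, and applying the same rule at any total outside the table, alpha is about 3% and power about 82%. With 18 evaluable patients, average power is about 77-78%.

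**The case against.** The strongest reply is that the protocol names 28 metastases as the number needed and gives the cut-off a few lines later, so the rule is naturally read as 24 of 28, with alpha 4.7%. On that reading the 20 patients are a loose recruitment figure. This stands in part. A reader might infer that the true type I error of Phase IIb is 16-22%, and the documents do not support that as an unconditional statement. It requires that all 20 patients are evaluable, that every metastasis is counted and that 24 is kept. The part above 16% also requires a distribution that the protocol does not give. Nor should one argue from a single metastasis per patient, where 24 successes could not be reached: that departs from the protocol's own 1.5.

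Second, patients without a hepatectomy are dropped, and rounding 18.7 up to 20 may leave room for that. This also stands in part. With 18 evaluable patients, alpha under the fixed cut-off returns to about 5-7%. But the protocol states no such allowance, and how many patients drop out is a matter of chance. With 19 evaluable, alpha is still 11-13%.

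Third, the steering committee may specify Phase IIb further, and a statistical analysis plan may exist. Neither removes the point. The committee's remit names no correction, and the protocol itself fixes a cut-off that does not match its own expected number of metastases. That goes beyond a detail left for later.

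Fourth, section VI.3 calls the analysis mainly descriptive, and the treated liver is resected in any case. This is fair as to harm: a wrong decision here would not change a participant's operation. It does not make the stated error rates correct.

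**Conclusion.** The concern holds in a conditional form. The (28, 24) design is right, but its error rates belong to exactly 28 metastases, and the enrolment plan leads to an expected 30 with no rule for the difference. On the protocol's own figures, with all 20 patients evaluable, 30 metastases counted and 24 kept, alpha is 16.0%, about three times the stated 5%. It is 9.3% at 29 and 24.5% at 31. The 20-22%, 11-13% and 5-7% figures for 20, 19 and 18 evaluable patients rest on the two assumed distributions. In the other direction, power is below the stated 80% at any number under 28.

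All figures assume independent metastases. Positive correlation within a patient would raise alpha further and is a separate matter.

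**What to change.** In section VI.1.b, state that the cut-off of 24 applies to 28 metastases, and add one of the following:

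1. Test the first 28 consecutively treated metastases and describe any later ones. This still needs a cut-off for a total below 28, such as 24/27 or 23/26.
2. Tie the cut-off to the number treated: 23/26, 24/27, 24/28, 25/29, 26/30, 27/31, 28/32, 28/33, 29/34, with the same 5% rule for any other total.

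Either way, say that alpha stays at or below 5% for each attained number but that 80% power is not met at every one: it is 72% at 27 and 79% at 32. Under option 2 the average power is about 82% with 20 evaluable patients and about 77-78% with 18, on the assumed distributions.

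The cost is one sentence or a short table in the protocol, with no extra patients and no extra data. It should be settled before Phase IIb results are known.

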## **VI.2. Definition of the studied population**

In each phase, the primary and secondary endpoints analyses will concern the population assessable for clinical feasibility, tolerance and accuracy to target CLM with HIFU. This population will consist in all patients included and which could have undergone a hepatectomy. Only those which could not have will be dropped out.

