### **II.3. Benefit / risk ratio**

The principal objective of the study is to confirm the results given in the pig model in human liver. It is important to remind that former experiments were well tolerated.

The study participants cannot expect any personal benefit from their participation.

However, to avoid any problem, it has been decided to test it in patient undergoing a curative operation for CLM. The surgical procedure to cure these patients' candidates to a liver resection will be totally identical to the one they would have undergone if not included in the study. The only difference will concern HIFU shootings on the healthy or peritumoral liver (depending on the study phase). These shootings will be performed, on liver to be resected, only after ultimate checking of indication and immediately before the resection phase. Thus, there is no risk to generate HIFU hurts on a healthy liver part that would not have to be resected.

The duration of the procedure of HIFU shootings will have to prolong the surgical operation of no more than 30 minutes. (Phase I main assessment criteria).

The principal potential risk to which could be exposed the patients of the study would be a hurt of surrounding organs secondary to HIFU shootings. This risk will be, of course, estimated after each shooting and this all through the study. Safety measure will be taken with particular care to avoid any accident: compresses will be put under the targeted area to limit risks of ultrasound propagation, and the shootings axis will not point towards noble intra-abdominal organs.

The post operative follow-up period will last 30 days, which seems to be enough time to report possible late AE. In that case, total care will be given until total remission or at least stabilization of adverse events.

Besides, the patients' enrolment will be divided into steps including from 2 to 4 participants (depending on the study phase). The decision to proceed to next steps will be taken by an independent Steering committee after considering all the study results. Naturally, the study could end prematurely due to SAE or accident.

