### **IV.2.c. Surgical procedures**

Once liver fully freed and indication of liver resection checked, prior to undertake any specific procedure regarding liver resection, the investigator surgeon will perform the shootings on the dedicated part of the liver.

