#### IV.4. Exclusion criteria during the study

A patient can be excluded of the study for one or several reasons:

- On sponsor or investigator decision,
- Withdrawal of his or her consent, or opposition to receive treatment,
- Inability to continue study (impossibility to carry out the hepatectomy, perioperative contraindication, intercurrent disease, worsening of clinical state, administrative reasons...)
- No news of the patient (lost to follow up),
- Patient's death.

Except in the last 2 cases, a final evaluation must be done, establishing the reasons why patient has to be dropped out.

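### Restricting every endpoint to patients who had a hepatectomy drops a patient whose resection is abandoned because of HIFU, and biases feasibility, safety and tolerance towards the device

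*Protocol*

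**What the plan says.** Protocol VI.2 sets one population for each phase: "the primary and secondary endpoints analyses will concern the population assessable for clinical feasibility, tolerance and accuracy". It defines that population in these words: "This population will consist in all patients included and which could have undergone a hepatectomy". It then adds: "Only those which could not have will be dropped out". The synopsis (Statistical methods) puts it as a completed fact: "This population concerns all the patients included in the study and who underwent a hepatectomy". Neither place makes an exception for a patient who has already received HIFU, and the protocol defines no separate exposed or safety population.

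The order of events is fixed elsewhere. Under IV.2.c, "prior to undertake any specific procedure regarding liver resection, the investigator surgeon will perform the shootings on the dedicated part of the liver". Under II.3, the shots are given "only after ultimate checking of indication and immediately before the resection phase". The same section says that the principal potential risk "would be a hurt of surrounding organs secondary to HIFU shootings". Section IV.4 foresees patients who cannot continue, and its reasons include "impossibility to carry out the hepatectomy, perioperative contraindication, intercurrent disease, worsening of clinical state".

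**The concern.** Completing the hepatectomy is a post-treatment event, and one that the device can prevent. Resectability is checked before the first shot, so a resection that is lost after that check is lost during or after device use. If the reason is a HIFU injury or haemodynamic collapse, the rule in VI.2 removes the patient from the very endpoints meant to record that harm.

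Safety and tolerance are primary in phase I (III.1) and secondary in phases IIa and IIb (III.2.a, III.2.b). Feasibility is also primary in phase I. Most of what these endpoints need is seen in theatre, so the need for a resected specimen does not justify the restriction. The bias can only favour the device. This is a first-in-human evaluation with six patients in phase I, where a single patient can decide the outcome.

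**Working it through.** **Inputs.** Phase I rule (VI.1.a): stop if both of the first 2 patients fail; otherwise treat 4 more and stop at 3 or more failures in 6. A failure is any of: overtime above 30 minutes, inability to shoot at the surface and/or in depth, an asepsis lapse, injury of a nearby organ, or a change of at least 10% in vital signs. The population is that of VI.2. The protocol gives no stopping probabilities for this rule, so there is no figure of its own to reproduce. Its phase IIb sample size does reproduce (28 metastases, at least 24 successes: exact one-sided alpha 4.7%, power 85.8%), but this point does not rest on it.

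**Step 1: single cases.** Suppose one phase I failure is a HIFU injury that prevented hepatectomy.
- 3 failures in 6, with the stop rule not met at the first look: the full count is 3/6, stop. After the drop it is 2/5, fewer than 3, continue. If the patient is replaced, the count stays at 2/6 (continue) when the replacement succeeds and returns to 3/6 when the replacement fails.
- Both of the first 2 fail: the full count is 2/2, stop. After the drop there is 1 failure, and the study continues.
- The injury is the only failure in 6: the reported rate is 0/5 (exact 95% CI 0 to 52%) instead of 1/6 (0.4 to 64%).

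**Step 2: stopping probability when nobody is dropped.** With true failure rate p and X the number of failures among the 4 later patients,

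P(stop) = p² + 2p(1−p)·P(X ≥ 2) + (1−p)²·P(X ≥ 3).

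At p = 0.30: 0.0900 + 0.42 × 0.3483 + 0.49 × 0.0837 = 0.0900 + 0.1463 + 0.0410 = 0.277.

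**Step 3: stopping probability under VI.2.** Let d be the share of failures that lose hepatectomy, and assume that dropped patients are replaced. Both are assumptions: the protocol gives neither a value for d nor a replacement rule. The failure rate among counted patients becomes

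p′ = p(1−d) / (1−pd),

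which goes into the formula of step 2. At p = 0.30 and d = 1/3: p′ = 0.20/0.90 = 0.222, and P(stop) = 0.0494 + 0.0746 + 0.0221 = 0.146.

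| True failure rate | d = 0 | d = 10% | d = 25% | d = 1/3 | d = 50% |
|---|---|---|---|---|---|
| 15% | 5.9% | 4.8% | 3.3% | 2.5% | 1.4% |
| 30% | 27.7% | 23.8% | 17.8% | 14.6% | 8.6% |
| 50% | 67.2% | 62.3% | 53.4% | 47.6% | 34.2% |

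The column d = 0 is also the result after the fix. If no exposed patient loses hepatectomy, the rule has no effect.

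**The case against.** The clause has a sensible purpose. Patients are included up to a month before surgery (IV.2.b), and resectability is confirmed at laparotomy before any shot. The ordinary patient without hepatectomy was never exposed, and dropping that patient does no harm to safety or tolerance. The accuracy and margin endpoints also need a resected specimen. All of this stands, but it does not justify applying the same restriction to exposed patients for feasibility, safety and tolerance.

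The stopping count may not follow VI.2 at all. VI.1.a speaks of failures noticed after 2 and after 6 patients and names no population, and VIII.5 places the statistical analysis at the end of the study. This stands in part. The effect on the count is the natural reading, because the failure criteria are the phase I primary endpoints that VI.2 restricts, but it is an inference.

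A reader might infer that such an injury would go unseen by those who decide. The protocol does not support that. Serious adverse events are notified for every included patient from consent to 30 days after surgery (V.1.b), excluded patients have a final evaluation except after death or loss to follow-up (IV.4), and the Steering committee considers all results and must agree to phase II (II.3, VI.1.a). These safeguards inform the decision. They do not restore the patient to the reported endpoint or to the pre-specified count.

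A reader might also extend the argument to the groups of three in phase IIa. That does not hold: the rule in VI.1.b counts only inaccurate shooting, so organ injury and vital signs do not enter it.

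Finally, most phase I failure criteria, such as overtime or an asepsis lapse, would seldom cancel a hepatectomy. A large d is therefore unsupported, and the one-third column should not be read as an estimate.

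**Conclusion.** The population rule is wrong for feasibility, safety and tolerance in all phases. It conditions on an event that follows HIFU and that HIFU can cause, and the resulting bias favours the device. This conclusion rests only on the wording of VI.2 and the synopsis and on the stated order of shots and resection.

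For the phase I count the point is plausible rather than stated. If VI.2 governs it, one dropped failure can turn a stop into a continuation. How much this matters on average depends on d and on replacement, both assumed: at a true failure rate of 30% the loss in stopping probability is about 4 percentage points at d = 10% (27.7% to 23.8%) and about 19 at d = 50% (27.7% to 8.6%). Nothing in the protocol shows where in that range the truth lies, and the event may never occur.

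The protocol supports neither a claim that the harm would be hidden from oversight nor a rule that scores every patient without an assessable specimen as a failure. The latter would mix loss of pathology with failure of the device, and in phase IIb the unit of analysis is the metastasis, not the patient.

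**What to change.** Reword VI.2 and the synopsis so that:
- feasibility, safety and tolerance, in all phases, are analysed in every patient in whom HIFU was started or attempted, with or without hepatectomy;
- only patients whose resection was cancelled before any HIFU attempt are excluded from these analyses;
- the phase I failure count in VI.1.a is stated to use this population;
- the specimen-based accuracy (IIa) and margin (IIb) endpoints stay in resected patients or metastases, with exposed but unresected patients reported alongside them, with the reason.

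The change is one of wording and needs no new data and no more patients. Its downside is that an event in an exposed patient whose resection was abandoned for an unrelated reason enters the device's count. That error is conservative, and reporting the reason makes it visible.
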